## Abstract

**Introduction:**

The workforce shortage in the healthcare context is a growing issue that exerts detrimental effects on employees (e.g., higher workload) and patients (e.g., suboptimal patient care). Since traditional approaches alone may not be enough to solve this problem, there is a need for complementary innovative digital health solutions, such as socially assistive robots. Hence, the proposed study aims to investigate the effects of gamified nursing education and physiotherapy delivered by a socially assistive robot on patient- (engagement, perceived quality of care) and employee-related outcomes (perceived self-efficacy, workload).

**Methods and analysis:**

Approximately 90 vascular and thoracic surgery patients will receive either standard care or standard care with additional robot interactions over the course of 3–5 days. Additionally, approximately 34 nursing and physiotherapeutic employees will fill out self-report questionnaires after weeks of not using a social robot and weeks of using a social robot. The main hypotheses will be tested with mixed-design analyses of variance and paired-samples *t*-tests.

**Discussion:**

While the proposed study has some limitations, the results will provide high-quality and comprehensive evidence on the effectiveness of socially assistive robots in healthcare.

**Ethics and dissemination:**

The study was approved by the Medical Ethics Commission of the University Medical Center and registered in the ISRCTN registry (ISRCTN96689284). The study findings will be summarized in international peer-reviewed scientific journals and meetings and communicated to relevant stakeholders.

## Introduction

The workforce shortage is one of the main challenges faced by the current healthcare system; for example, only in the United Kingdom, the National Health Service reported a workforce shortage of around 100,000 employees in 2019 (1). These numbers, particularly the demand for nurses, are projected to increase due to various reasons, most notably due to population aging (2). The National Health Service estimates that shortages could grow up to 200,000 by the middle of the decade and at least to 250,000 by 2030 (1). Naturally, workforce shortage, together with increasing demands and having to take care of patients who are sicker than in the past (due to reduced patient length of stay), leads to a higher workload of the existing staff (2). On the provider side, this creates a vicious circle; increased workload negatively affects job satisfaction, increases burnout and turnover, and thus additionally contributes to the shortage of employees (3, 4). On the end-user side, employees’ higher workload is associated with suboptimal patient care and may lead to reduced patient satisfaction (4, 5). As a higher workload can lead to omissions of essential nursing care (6), nursing tasks that are generally not a priority, but are important nonetheless, can suffer even more (7). Such overlooked tasks may include educating patients, increasing patients’ health literacy, engaging in non-critical communication, and empowering patients to take a more proactive role in decision-making.

Considering that achieving active patient engagement and self-management is one of the leading healthcare goals of the twenty-first century (8, 9) and that the already overworked staff cannot always sufficiently fulfill this goal, there is a need for innovative solutions that may complement the existing approaches (for example, hiring additional nurses may only help to a certain extent, as the nursing schools are not able to keep up with the increasing educational demand (10)). The gap may be reduced with digital health approaches, which refer to the use of information and communications technologies in medicine and other health professions. Digital health can involve both hardware and software solutions and may serve different functions, including improving the quality of care, providing more personalized healthcare to patients, and improving the overall patient and staff experience (11). While “digital health” is generally a very broad term, socially assistive robots, i.e., robots that assist human users through social interaction, seem to be a particularly promising technology-based solution in this context (12). First, they were designed to provide education, feedback and support, coach patients through tasks, and serve the role of a companion (12–14). Second, many socially assistive robots are equipped with multimodal sensing and can thus collect a wide array of data that can be used for personalizing healthcare and individualized responding to patients’ needs and demands (15). Third, social robots can be developed in a way that facilitates patients’ motivation, learning, and confidence, for example, via integrating elements of gamification (16). Lastly, socially assistive robots can physically interact and work with humans while being immune to diseases such as COVID-19, demonstrating their suitability for situations that require physical distancing and isolation (17).

While hospitals and other healthcare institutions are increasingly adopting socially assistive robots (18, 19), research on their effects on patients and staff is scarce yet promising. In fact, the existing empirical studies suggest that socially assistive robots, if implemented properly, can positively impact patient engagement, satisfaction, and wellbeing (20–22). Furthermore, many healthcare workers perceive social robots as a tool that could alleviate their workload by supporting them to provide better care to older people [e.g., via assisting with medication, providing information, and fetching things (23)]. There is also tangible evidence that placing robots in healthcare institutions can help reduce staff workload (20, 24, 25). However, the generalizability of these studies is somewhat limited as they often employ rather rudimental methodological approaches and relatively small and specific samples, such as the elderly with dementia and children with neurodevelopmental disorders (12, 26–28). Moreover, to our best knowledge, no study has specifically tested the effects of using a socially assistive robot capable of delivering gamified nursing education and general/respiratory physiotherapy.

Hence, the present study, carried out within the H2020 HosmartAI project, aims to investigate the effects of a socially assistive robot Pepper (29)—that will be deployed on vascular and thoracic surgery wards and, at this stage, be partially operated and supervised by humans—on a wide array of patient- and employee-related outcomes.

As socially assistive robots can provide education without the usual restraints imposed upon human employees (e.g., the robot can effortlessly repeat the same instructions multiple times) and in a gamified manner that may facilitate motivation and learning, we expect positive effects of interactive digital assistance on patient-related outcomes. More specifically, we hypothesize that patients will exhibit higher levels of patient engagement (H1) and perceived quality of medical care (H2) after being subjected to standard care with additional gamified nursing education and general/respiratory physiotherapy (delivered by a socially assistive robot) compared to levels at the beginning of the study. Furthermore, we hypothesize that patients exposed to standard care with additional gamified nursing education and general/respiratory physiotherapy (delivered by a socially assistive robot) will experience larger improvement of patient engagement (H3) and perceived quality of medical care (H4) compared to patients exposed solely to standard care (human interaction only). Additionally, due to socially assistive robots’ potential to be involved in patient care and help with some of the work tasks, we hypothesize that employees will exhibit higher self-efficacy (H5) and experience lower workload (H6) during time periods when a socially assistive robot is deployed compared to time periods when a socially assistive robot is not deployed.

In addition to our primary hypotheses, we aim to determine the percentage of non-urgent communication taken up by the social robot (RQ1), the amount of employees’ time saved by such robot-human interactions (RQ2), and the extra time of interaction provided to patients by using a socially assistive robot (RQ3). We are also interested in how these variables (e.g., the number/percentage of AI interactions) correlate with both patient- and staff-related outcomes (RQ4). Lastly, we are also interested in patients’ user experience concerning the use of a socially assistive robot (RQ5). Answering these research questions and testing the hypotheses stated above will generate a novel and comprehensive insight into the effectiveness of using socially assistive robots in healthcare.

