### Study design

The proposed study employs a between-within interaction design with multiple iterations. Patients and employees participating in the study will be recruited in a University Clinical Centre Maribor, Slovenia. The study will be carried out in 1-week intervals, followed by a 1-week washout period between each iteration. Overall, the study will be conducted over 2 years or less if the desired sample size is reached sooner.

Patients admitted to vascular and thoracic surgery wards for an elective (non-emergency) procedure will be screened for eligibility regarding the inclusion and exclusion criteria. Eligible participants will then be informed about the study characteristics and asked to fill out an informed consent form. Those who will consent to participate in the study will participate for 3–5 days. Depending on the week (see Figure 1), participants will be allocated to the standard care group (i.e., a control group that will not interact with a socially assistive robot) or standard care group with additional robot interactions. Participants from both groups will first be informed about the study and fill out the baseline questionnaires (demographic data, engagement, and perceived quality of care). Similarly, participants from both groups will be subjected to standard nursing education and general/respiratory physiotherapy delivered by nursing and physiotherapy staff. However, the patients allocated to the standard care group with additional robot interactions will additionally be subjected to nursing education and general/respiratory physiotherapy delivered by a socially assistive robot. Moreover, they will be able to call the robot for additional assistance (not related to nursing education and physiotherapy) during the whole study period. At the end of their participation, patients from both groups will be asked to fill out the questionnaires (engagement, perceived quality of care) for the second time. Patients from both groups will also be asked to rate the education and physiotherapy they received during the study period. Moreover, patients that will interact with a socially assistive robot, will also fill out the User Experience Questionnaire (30) at the end their participation.

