### Data analysis

#### Preliminary analyses

We will use the IBM SPSS Statistics 28 program for statistical analysis. In the first step, we will clean the dataset and exclude all participants with more than 20% of missing values within any questionnaire. The remaining missing data will be analyzed to determine whether they are missing completely at random and, in case this is confirmed, replaced using the expectation-maximization algorithm. We will also perform basic psychometric analyses of the questionnaires, namely the analysis of reliability as internal consistency (coefficient α), and calculate the factor scores in accordance with the scoring instructions.

In the next step, we will perform basic descriptive analyses (means and standard deviations) and check the assumptions of the chosen statistical tests (such as the normality of the distribution assumption). This step will be followed by correlational analyses (to establish relationships between different variables) and inferential tests, whereby results with a *p*-value below 0.05 will be considered statistically significant.

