#### Analyses of patient-related outcomes

The patient-related outcomes, specifically patient engagement (H1, H3) and perceived quality of care (H2, H4), will primarily be analyzed with two separate mixed-design (split-plot) analyses of variance (ANOVA), with group as the between-subjects factor (2 groups: standard care, standard care with robot interactions) and time as the within-subjects factor (2 levels: T1 and T2; see Figure 1). Significant results will be followed up with *post hoc* tests using the correction to adjust for multiple testing. All results will be accompanied by effect sizes.

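### H1 and H2 are primary claims about the robot but are uncontrolled before-after changes that the named ANOVA does not test; H3 to H6 carry no stated multiplicity control

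*Protocol article*

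**What the plan says.** The Introduction expects positive effects of robot assistance on patients and then spells these out. H1 and H2 state that "patients will exhibit higher levels of patient engagement (H1) and perceived quality of medical care (H2) after being subjected to standard care" with robot-delivered education and physiotherapy added, "compared to levels at the beginning of the study". H3 and H4 state that the improvement will be larger "compared to patients exposed solely to standard care (human interaction only". H5 and H6 concern staff self-efficacy and workload. The next paragraph opens "In addition to our primary hypotheses, we aim to determine", so all six hypotheses are primary, and none is ranked above another.

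Study design says that both arms receive the standard education and physiotherapy from staff, and that the robot arm receives the robot sessions on top.

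Under Analyses of patient-related outcomes, "patient engagement (H1, H3) and perceived quality of care (H2, H4), will primarily be analyzed with two separate mixed-design (split-plot) analyses of variance", with factors group (2) and time (2). It continues "Significant results will be followed up with" post hoc tests, with a correction for multiple testing that is not named. Staff outcomes get two paired t-tests. Preliminary analyses sets the general rule for inferential tests: a p-value "below 0.05 will be considered statistically significant".

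Participants and recruitment bases the patient sample size on the within-between interaction (f = 0.15, about 90 patients) and the staff sample size on a paired t-test (d = 0.50, at least 34).

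**The concern.** A change from start to end of a 3 to 5 day surgical stay can come from routine teaching, from recovery, or from answering the questionnaire a second time. All of these act in the robot arm whether or not the robot helps. H1 and H2 have no comparator to remove them, yet they are introduced as effects of the robot and have the same primary status as the controlled hypotheses H3 and H4. The trial could therefore report two primary successes for the robot while both interactions are null.

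There is also a mismatch between hypothesis and test. A 2 x 2 mixed ANOVA gives three F-tests: group, time averaged over both arms, and group by time. None of them is the T1-T2 change in the robot arm. If the time effect is read as the test of H1, the control arm contributes half of the answer. If the robot-arm contrast is instead taken as a post hoc test, a primary hypothesis depends on a follow-up that is not named and is run only after something else is significant.

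The third part is multiplicity. The one stated correction covers post hoc tests. None is stated across the two interactions or across the two staff t-tests.

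**Working it through.** **Reproducing the plan's figures.** For the interaction, lambda = f² x N x m / (1 - rho), with m = 2 measurements and df = (1, N - 2). The article gives no correlation, so rho = 0.5 is assumed. With f = 0.15 and N = 90, lambda = 0.0225 x 90 x 2 / 0.5 = 8.1, and power is 80.4%. For staff, a two-sided paired t-test (sidedness assumed) with d = 0.50 and n = 34 has power 80.8%. Both stated sample sizes reproduce. The patient figure powers H3 and H4 only.

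**H1 when the robot does nothing.** Assumptions: an equal split of 90 gives 45 per arm; both arms have the same mean change, 0.3 or 0.5 SD of the change score; the true robot effect is zero. The article states no expected change, so these shifts are illustrative. The robot-arm test is a paired t-test with noncentrality shift x sqrt(45), that is 2.01 or 3.35. The gated figures are simulated (40,000 trials), with the gate being a significant time or interaction effect. The 0.025 level stands for a Bonferroni correction over two within-arm contrasts, an assumption because the correction is unnamed.

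| Test | Shift 0.3 SD | Shift 0.5 SD |
|---|---|---|
| Robot-arm change, two-sided 0.05, no gate | 50% | 91% |
| Robot-arm change, gated, at 0.025 | about 39% | about 84% |
| Group-by-time interaction (H3) at 0.05 | 5% | 5% |

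Correction lowers the first row only modestly, because the fault lies in the contrast and not in the alpha level.

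**The time effect is not H1.** Let only the control arm change, by 0.5 SD, and leave the robot arm unchanged. The pooled mean change is (0 + 0.5)/2 = 0.25 SD. Its test has noncentrality 0.25 x sqrt(90) = 2.37 on 88 df, and is significant in about 65% of trials. The robot-arm test rejects in 5%, as it should. A significant time effect can therefore appear when H1 is false.

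**Multiplicity for the four clearly unadjusted tests.** With all nulls true and the tests independent:
- two interactions and two t-tests: 1 - 0.95⁴ = 18.5%, about 19%;
- two tests within one population: 1 - 0.95² = 9.75%.

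**The case against.** Several counter-arguments have force.

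- **The controlled comparison is already planned.** H3 and H4 are the group-by-time interaction, and the study is powered on it. The Discussion also concedes that a larger randomized trial may be needed. This stands. It narrows the point to the primary status and unnamed contrast of H1 and H2. It does not remove the point, because H1 and H2 remain separate primary claims that can succeed when H3 and H4 fail.
- **The robot-arm contrast may be a corrected post hoc test.** This is a natural reading. For that reason, a reader who infers that all six primary hypotheses are judged at an unadjusted 0.05 goes too far: only H3 to H6 clearly are. It also follows that 1 - 0.95⁶ = 26.5% is not the plan's error rate. That figure needs six independent unadjusted tests, whereas H1 shares robot-arm data with H3, and H2 with H4.
- **If both arms improve, H1 as worded is true.** Correct, so the 50% and 91% are not type I error rates. They are the chance that a true but uninformative statement is available to be credited to the robot.
- **Multiplicity may be settled in an analysis plan that is not shown.** It may, and the 0.05 rule does not exclude that. But the article itself fixes the primary status of all six hypotheses, the 0.05 rule and the limit of the correction to post hoc tests.
- **The H2 baseline.** Patients "fill out the baseline questionnaires (demographic data, engagement, and perceived quality of care") before the study's education and physiotherapy, so one might infer that T1 and T2 rate different care and that H4 is biased. The documents do not support that. Study design says that questionnaire instructions will be adapted to the time periods, and the timing is the same in both arms.

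**Conclusion.** The point holds in two parts.

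First, H1 and H2 should not be primary hypotheses about the robot. They can be met with no robot effect, and the ANOVA named for them has no term that tests them. This follows from the text and needs no assumption. Its size depends on how much patients change under standard care, which the article does not give. With no robot effect and 45 per arm, a common change of 0.3 to 0.5 SD gives support for H1 in about 39% to 84% of trials on the gated, corrected route, and in 50% to 91% uncorrected.

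Second, H3 to H6 have no stated error control. The chance of at least one false claim is about 19% over the four tests, or 9.75% within each population, if all nulls are true and the tests are independent. Whether 19% or 9.75% is the relevant figure depends on whether patients and staff form one family or two, which the article does not say.

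Neither part undermines the planned interaction tests or the sample sizes. The risk is in what is claimed from the results, so the change should be made before analysis.

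**What to change.** 1. Make the group-by-time interactions (H3, H4) the only primary patient tests. They are the tests that the sample size already supports.
2. Move H1 and H2 to secondary or descriptive status. Name the contrast as the T1-T2 mean change, report it with a 95% CI in both arms, and draw no robot-effect claim from it. A secondary test of H1 and H2 is acceptable if the contrast is named in advance.
3. Declare patients and staff as two families and control error within each by a pre-stated procedure. A fixed sequence would do: H3 then H4 for patients, each at two-sided 0.05, and H5 and H6 in an order chosen by the sponsor.
4. State that alpha is 0.05 per family and not study-wide. Two independent families at 0.05 still give up to 1 - 0.95² = 9.75% across the study.

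The sample size stays the same. By comparison, Bonferroni at 0.025 within each family would need 110 patients (rho = 0.5) and 41 staff, or would leave power at about 71% with 90 and 34. The cost of the sequence is that its second hypothesis cannot be claimed if the first fails. H1 and H2 also lose their primary status, a change to an approved and registered study that should be documented.

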Lastly, employees’ workload will be measured with the Nasa Task Load Index [NASA TLX (38)], a very brief and widely used scale that assesses the perceived workload. The scale consists of six items (e.g., “*Temporal demand*”), answered on a 7-point scale ranging from “*very low*” to “*very high*.” The first three items will be slightly adapted to reflect the work in general instead of any one particular task. While each item alone provides useful and relevant information about different aspects of subjects’ experiences, the items can be combined into an overall score (39). Previous studies support the notion that the NASA TLX is a reliable and valid instrument also in the healthcare context [coefficient α = 0.72 (40)].

Answering the secondary objectives will require the assessment of additional outcomes, in particular, the percentage of non-urgent communication taken up by the social robot, time saved by human-robot interaction, and extra time of interaction provided to patients. Patients’ user experience and their ratings of each of the two types of nursing education (human/AI) and physiotherapy (human/AI) will also be assessed.

Most of these outcomes will not be measured with self-report questionnaires. During iterations with a socially assistive robot, the patients will be able to call for additional assistance and choose between human or AI assistance (by using one of two call devices). The number of calls will be recorded automatically, enabling us to calculate the ratio during analyses. Similarly, the number of actual interactions and the time spent for each encounter (with a human or AI) will also be recorded. Patients’ ratings of nursing education and physiotherapy delivered by a human/robot will be measured with a handful of self-construed items. It is worth noting here that both patients and staff will also be asked to fill out basic demographic questions.

Furthermore, patients will also fill out the User Experience Questionnaire [UEQ (30)]—the most widely adopted measure of user experience, which is already available in Slovene (41). It contains 26 items (e.g., “*unlikable/pleasing*”), which can form different subscores (i.e., perspicuity, efficiency, dependability, stimulation, and novelty) and the overall impression of the product. The subscales as well as the overall scale exhibit satisfactory internal consistency (for the overall score: coefficient α = 0.89).

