#### Other analyses

The additional research questions will be answered descriptively (RQ1-RQ3, RQ5) or using the Pearson correlation coefficient (RQ4).

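### RQ4 relates robot interaction counts and total minutes, collected over unequal windows of 3 to 5 days, to patient outcomes by an unadjusted Pearson correlation, so these measures partly reflect days of participation

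*Protocol article*

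**What the plan says.** The Introduction of the protocol article lists RQ4 among the additional research questions: "We are also interested in how these variables (e.g., the number/percentage of AI interactions) correlate with both patient- and staff-related outcomes (RQ4"). The variables meant are those of RQ1 to RQ3: the share of non-urgent communication taken up by the robot, employee time saved, and extra interaction time for patients. Under Other analyses, RQ4 is to be answered "using the Pearson correlation coefficient (RQ4"). No covariate, partial correlation or per-day scaling is named.

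Study design sets the observation window: "Those who will consent to participate in the study will participate for 3–5 days". Within it, robot-group patients have open access: "they will be able to call the robot for additional assistance (not related to nursing education and physiotherapy) during the whole study period". Outcomes are taken when the window closes: "At the end of their participation, patients from both groups will be asked to fill out the questionnaires (engagement, perceived quality of care"). Measures describes how exposure is captured: "the number of actual interactions and the time spent for each encounter (with a human or AI) will also be recorded", and for calls, "The number of calls will be recorded automatically, enabling us to calculate the ratio during analyses".

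**The concern.** A count, or a sum of minutes, gathered over a window that differs between patients mixes two things: how intensively a patient uses the robot and how long the patient had it. At the same rate of use, a 5-day patient has 5/3 = 1.67 times the opportunity of a 3-day patient. An unadjusted Pearson r cannot separate the two. If days of participation also go with engagement or perceived quality of care, part of r comes from days.

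There is a second route. Patients choose between a human and an AI call device, so use is self-selected. Patients who are more engaged, or more satisfied, at baseline may use the robot more and also score higher at the end. This route is open to the percentage measure as well as to the counts.

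What is at stake is interpretation. A correlation between more robot use and better outcomes invites a dose-response reading that the raw r cannot carry.

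**Working it through.** **Plan's own figures.** The protocol gives no figure for RQ4. The patient sample size of about 90 reproduces if the T1–T2 correlation is taken as 0.5 (not stated): f = 0.15 gives noncentrality 0.15² × 90 × 2 / (1 − 0.5) = 8.1 and power 0.804. It matters here only for the size of the robot group, about 45 if the groups are equal (assumed).

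**Step 1: how far a count reflects days.** Assumptions, none from the protocol except the 3 to 5 day range:
- days D are uniform on 3, 4, 5, so E[D] = 4, Var(D) = 2/3, E[D²] = 16.67;
- counts are Poisson at mean rate λ per day;
- the rate varies between patients with coefficient of variation CV, independently of D.

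Var(count) = λE[D] + λ²Var(D) + (CV·λ)²E[D²], and corr(count, D) = λ·SD(D) / SD(count).

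With λ = 3, the numerator is 3 × 0.8165 = 2.449.

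| CV of rate | Var(count) | corr(count, days) |
|---|---|---|
| 0 | 12 + 6 = 18 | 2.449/√18 = 0.58 |
| 0.5 | 18 + 37.5 = 55.5 | 2.449/√55.5 = 0.33 |
| 0.8 | 18 + 96 = 114 | 2.449/√114 = 0.23 |

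Over rates of 1, 2 and 4 per day and CV from 0 to 1, the correlation runs from 0.18 to 0.63, so days explain about 3% to 40% of the variance of the count. Total minutes accumulate in the same way. Variation in encounter length, not modelled here, would lower the correlation somewhat.

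**Step 2: what reaches the outcome.** With no effect of use, the r induced through days is corr(count, days) × corr(days, outcome). The second factor is unknown.
- If it is 0, the induced r is 0.
- If it is 0.1 to 0.3 in size (assumed), the induced r is 0.18 × 0.1 = 0.02 up to 0.63 × 0.3 = 0.19.
- If it is −0.30 (assumed), the three rows above give −0.17, −0.10 and −0.07.

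By Fisher's z at n = 45, an induced r of 0.05, 0.10 or 0.20 lifts a nominal 5% two-sided error rate to about 6%, 10% or 26%.

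**Step 3: the percentage measure.** In a simulation with 3 calls per day in total and an AI share independent of days (both assumed), the percentage of AI calls had correlation 0.00 with days. The AI count in the same simulation had 0.32.

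**Step 4: the baseline route.** Assume corr(T1, use) = 0.3 and corr(T1, T2) = 0.5.
- Against the T2 score, r = 0.3 × 0.5 = +0.15 with no robot effect.
- Against change, with equal variances, corr(T1, T2 − T1) = (0.5 − 1)/√(2 × (1 − 0.5)) = −0.5, so r = 0.3 × (−0.5) = −0.15.

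The sign depends on which score is used. Adjusting for T1 deals with both cases.

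**Step 5: the two routes together.** If they are independent, the negative days route and the +0.15 baseline route sum to about −0.02, +0.05 and +0.08 for the three rows. Under these assumptions they partly offset each other.

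**The case against.** The case against has real force on four counts.

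- **The percentage is named alongside the number.** The Measures section also describes a ratio of calls. That measure is already normalised for time. This stands, and limits the days argument to counts and total minutes.
- **Confounding by length of stay is not shown.** A reader might infer that longer participation marks a harder surgical course and so biases RQ4. The protocol does not support this. It reports no link between days and either outcome, patients are elective, and those in an intensive step-down unit or regimen are excluded. The limitations paragraph of the Discussion mentions length of hospitalization only to explain short exposure.
- **RQ4 is descriptive.** The protocol claims no dose-response relation, and total exposure is a legitimate quantity in its own right. This stands as a reason for low severity. It does not make the raw r interpretable as an effect of use.
- **An article may leave the detail to a fuller plan.** The protocol does not say whether T2 or change scores enter RQ4, and that silence is no fault. The estimator, however, is stated. An unadjusted Pearson coefficient is a choice on the page, and a better one is available.

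A reader might also add the baseline route to the days route as if the two compounded. Under the illustrative values they have opposite signs.

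**Conclusion.** The point holds in a limited form and is minor. Interaction counts and total minutes partly measure days of participation: the illustrative correlation is about 0.2 to 0.6, resting on assumed uniform days, Poisson counts and 1 to 4 interactions per day. The RQ4 correlation for these measures can be distorted if days also relate to the outcome. The size would be about 0.02 to 0.19 for an assumed days–outcome correlation of 0.1 to 0.3, and zero if there is none. The percentage of AI interactions escapes the days problem but, like the counts, may reflect baseline engagement or perceived quality because use is self-selected.

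It would go too far to say that RQ4 as a whole is confounded by length of stay, or that the trial's main conclusions are affected. RQ4 is exploratory and lies outside H1–H6 and the sample size calculation.

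**What to change.** For patient outcomes in RQ4, among robot-group patients:

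- **Interaction count and total minutes:** report the partial correlation with the T2 score, adjusted for the T1 score and days of participation. Alternatively, use per-day rates adjusted for T1. One or the other is enough; dividing by days and also adjusting for days is not needed.
- **Percentage of AI interactions:** report the partial correlation with T2, adjusted for T1 only.
- **Skewed use:** use a rank-based version.
- **Raw Pearson r:** keep it as descriptive only, and state that no dose-response conclusion will be drawn from it.

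T1 scores are already collected. Days of participation are not listed as a variable but should be derivable from the dates of the two questionnaires.

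The cost is at most two degrees of freedom. With 45 patients (equal groups assumed) they fall from 43 to 41. Using r = t/√(df + t²), the two-sided 5% critical value moves from 2.017/√(43 + 4.07) = 0.29 to 2.020/√(41 + 4.08) = 0.30.
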